## Analysis Plan and Outcomes.

Primary outcome is the provider-specific SAR, separately for each antibiotic grouping. Secondary outcomes include CD, readmission (< 30 days of discharge), length of stay. Changes in 2-month SAR will be estimated using an interrupted time series analysis, evaluating changes in each antibiotic grouping separately, analysis will consider hospital fixed effects. Secondary outcomes will be analyzed at the patient level among all billed encounters using logistic or negative binomial regressions. Inclusion of provider and quarter-year fixed effects will control for time-invariant provider and site characteristics and secular time trends (e.g., seasonal patient mix) and establish a difference-in-difference framework. This approach will estimate the within-provider change in patient outcomes, pre- and post-intervention. We will control for patient (e.g., sex, age, Comorbidity Index) mix, time-variant provider (e.g., census) factors.

Data Sources: The primary source of data will be the EH Clinical Data Warehouse (CDW), a repository that integrates data from multiple clinical applications within EHC and has flexibility to create customized, research-specific metrics. Outcomes for Aim 2 will also be calculated from data elements within the EH CDW (i.e., re-admissions, length of stay.)

Provider-specific SARs. Data elements will be aggregated into 2-month intervals for each of the 147 hospitalists across each hospital. Billed Days of Therapy (bDOT) and billed patient-days (bPD) derived for each antimicrobial group will be limited to the eligible dates of each patient encounter to dates billed by a hospitalist (bPD). For each period, a SAR will be determined from provider specific bDOT calculated along with predicted DOT using preliminary regression models. Regression models will be created from analyzing summary provider specific data and providers' encounter data for each 2-month period of the baseline period. Encounter summary data will be aggregate number of encounters billed by

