#### **5. Study Measures and Outcomes**

Data from January 2023 to December 2024 will be extracted for inpatients at all hospitals with Hospital Medicine Services. For each hospitalist, billing data will be used to identify patient encounters and to calculate billed patient-days (bPD). Antibiotic prescribing data from electronic medication administration records (eMAR) will capture days of antibiotic therapy (DOT) for NHSN-defined broad-spectrum hospital-onset (BS-HO) agents per bPD.

Patient characteristics linked to each encounter will include age, microbiology results (e.g., bacteremia), ICD-10–based antibiotic indications (e.g., pneumonia, COVID-19, sepsis, urinary tract infection), and comorbidities, enabling calculation of Elixhauser comorbidity indices. Generalized linear models will be used to generate provider-level observed-to-expected ratios (OERs). In each model, bPD will remain continuous, while other predictors will be categorized by quintiles based on their relationship with DOT. Based on input from Hospital Medicine Services leadership and focus groups, hospital-specific models will be used to calculate OERs in order to maximize provider credibility of the metric.

The primary outcome will be the observed provider-specific antibiotic prescribing rate, defined as billed DOT of BS-HO antibiotics per 1,000 billed patient-days. This measure alone will not be risk adjusted; however, patient- and provider-level characteristics will be adjusted for and included as covariates in the regression model described below. For illustrative (descriptive) purposes, risk-adjusted provider-specific OERs will also be estimated, with point estimates (means) and variance plotted over time by facility. OERs will not be modeled directly as regression outcomes.

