## **7. Statistical Analysis**

**For the primary outcome analysis,** a generalized linear mixed-effects model with a negative binomial distribution and log link will be used to evaluate the effect of the intervention on antibiotic prescribing rates over time. The observed DOT will be modeled as a function of provider receipt of feedback reports, time (bimonthly period) to account for secular trends and time-varying confounding, and a random facility effect to account for clustering of providers within hospitals. A random intercept for each provider nested within facility will be included to account for correlation among repeated observations and the hierarchical data structure. The intra-cluster correlation coefficient (ICC) will be estimated to quantify the proportion of total variance attributable to between-cluster differences. Models will adjust for patient-mix characteristics as covariates.

Sensitivity analyses of the primary outcome will be conducted among the subset of providers who indicate that they received and reviewed the feedback reports, to account for potential implementation bias.

**Secondary outcomes will be analyzed at the patient level** among all patients receiving care from hospital medicine services and discharged with ICD-10 codes for pneumonia or urinary tract infection, as this group is expected to be most vulnerable to changes in antibiotic de-escalation practices. Safety outcomes will be analyzed using generalized mixed-effects logistic regression models to evaluate intervention effects over time, accounting for repeated hospitalizations within patients and clustering by facility. Covariates will include time (to account for seasonality) and patient-level indicators (COVID-19, influenza, Elixhauser comorbidity index, and sepsis). All analyses will be performed using R Statistical Software (version 4.2.0; R Core Team, 2021).

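### The SAP's listed covariates for the safety models omit age, which is linked to every encounter, so a change in age mix at one hospital around its crossover would bias the safety odds ratios, modestly

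*Combined protocol and SAP*

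**What the plan says.** SAP section 7 describes the safety analysis as follows: "Safety outcomes will be analyzed using generalized mixed-effects logistic regression models to evaluate intervention effects over time, accounting for repeated hospitalizations within patients and clustering". The clustering unit is the hospital. It then gives the adjustment set: "Covariates will include time (to account for seasonality) and patient-level indicators (COVID-19, influenza, Elixhauser comorbidity index, and sepsis". Neither age nor sex appears, and no reason is given.

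SAP section 5 shows that age will be available: "Patient characteristics linked to each encounter will include age, microbiology results (e.g., bacteremia" and so on. The same sentence ends "and comorbidities, enabling calculation of Elixhauser comorbidity indices". Age is therefore named separately from the comorbidities that feed the index. Sex is not named there.

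The protocol (Analysis Plan and Outcomes) plans a different model for its secondary outcomes: "Secondary outcomes will be analyzed at the patient level among all billed encounters using logistic or negative binomial regressions". On adjustment it says "We will control for patient (e.g., sex, age, Comorbidity Index) mix, time-variant provider (e.g., census) factors".

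The outcome lists differ too. The protocol (Study Endpoints; Analysis Plan and Outcomes) names C. difficile infection, readmission and length of stay. SAP section 6 adds in-hospital mortality and turns length of stay into a binary outcome, more than 7 days.

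**The concern.** The safety models support the SAP's aim of changing prescribing without harming patients (SAP section 1). Age is plausibly related to all four outcomes. It is fixed before exposure, so adjusting for it does not condition on anything the intervention can alter.

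Only four hospitals are randomised, and only in their order. That cannot be relied on to balance changes in patient mix within a hospital over time. Facility terms absorb differences that stay constant, and period terms absorb changes shared by all hospitals. What remains is a change in age mix specific to one hospital. At crossover it would be read as an intervention effect. While the hospital is still in the control condition, it could hide harm.

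Such a change is possible because the safety cohort is selected on discharge codes for the conditions that the crossover education session addresses, so diagnosis or coding habits could move with the intervention. The documents do not show that this will happen.

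**Working it through.** The plan states no figure for this point, so there is nothing to reproduce. The check asks how far the intervention odds ratio moves when its true value is 1.00 and age is left out.

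**From the SAP.** Four hospitals in the full analysis; 12 two-month periods from January 2023 to December 2024; Figure 1 has hospitals A to D crossing over in July, September and November 2023 and January 2024, that is, at periods 4, 5, 6 and 7.

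**Assumed, not in the documents.** Age SD 15 to 17 years; outcome odds ratio 1.2 to 1.8 per 10 years of age; outcome risk 3 to 15%; shift in mean age 1 to 3 years. Hospital is fitted as a fixed effect, as an approximation to the SAP's facility clustering. No other covariate is included.

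**Step 1: weight of each hospital.** Let X be 1 when hospital h is exposed in period t. Remove hospital and period effects: R = X − (hospital mean) − (period mean) + (overall mean). The hospital means are 9/12, 8/12, 7/12 and 6/12; the overall mean is 30/48 = 0.625. Summing R over each hospital's exposed periods:

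- A: 0.625 + 0.375 + 0.125 − 6 × 0.125 = 0.375
- B: 0.458 + 0.208 − 6 × 0.0417 = 0.417
- C: 0.292 + 6 × 0.0417 = 0.542
- D: 6 × 0.125 = 0.750

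The total is 2.083, so the weights are 0.18, 0.20, 0.26 and 0.36. The text of SAP section 3 puts the last crossover by March 2024, later than Figure 1 shows. With that date the weights are 0.17, 0.20, 0.26 and 0.37, so the result hardly depends on which is meant.

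**Step 2: approximate bias.** For a shift of d years at hospital h from its crossover, spurious OR ≈ exp(weight × d/10 × ln(OR per 10 years)).

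- Smallest case, A, 1 year, OR 1.2: exp(0.18 × 0.1 × 0.182) = 1.003
- D, 3 years, OR 1.6: exp(0.36 × 0.3 × 0.470) = 1.052
- D, 3 years, OR 1.8: exp(0.36 × 0.3 × 0.588) = 1.066
- D ageing 3 years from period 4, while still in control (weight −0.18), OR 1.6: exp(−0.18 × 0.3 × 0.470) = 0.975

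**Step 3: large-sample logistic fit** with hospital and period effects, 1- to 3-year shifts, OR 1.2 to 1.6 per 10 years, age SD 15, 5% risk:

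| Change in mean age | Spurious OR |
|---|---|
| Constant differences between hospitals | 1.000 |
| Drift common to all hospitals | 1.000 |
| First hospital only, at its crossover | 1.003 to 1.025 |
| Last hospital only, at its crossover | 1.007 to 1.053 |
| Last hospital only, while still in control | 0.997 to 0.976 |
| Every hospital, at its own crossover | 1.018 to 1.147 |

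A fall in age reverses the direction. At OR 1.8 and a 3-year shift, the last-hospital figure is 1.06 to 1.07 and the every-hospital figure about 1.18. Outcome risk makes little difference. With age in the model, the odds ratio returned to 1.000 in all six rows at the largest setting tested (3 years, OR 1.6, 5% risk). That fit used the linear age effect under which the data were generated.

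**Step 4: the time term.** SAP section 7 ties time in the safety models to seasonality, whereas the primary model uses the bimonthly period. If only season were fitted, a common drift of 1 to 3 years over the study would also leak in: 1.009 to 1.071.

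**The case against.** The strongest reply is that the effect is small and the inputs are assumed. Both are true. One hospital shifting by one year moves the odds ratio by about 0.3 to 2% over the whole assumed range. The calculation also leaves out the covariates that the SAP does specify. Comorbidity rises with age, so the Elixhauser index would absorb part of any shift.

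A reader might infer that the protocol already requires age and sex in all four safety models and that the SAP departs from it. The documents do not support that. The protocol's list is illustrative, and it belongs to a model on all billed encounters with provider and quarter-year fixed effects. In-hospital mortality is an outcome only in the SAP. For sex, the protocol's example is the only support.

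A reader might also infer that leaving out age dilutes a true effect. With age SD 17 years, mortality of 3 to 8% and age odds ratios of 1.3 to 1.8 per 10 years, a conditional odds ratio of 1.30 would appear as 1.27 to 1.30. This is the usual difference between conditional and marginal odds ratios (non-collapsibility), not bias.

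Two further replies carry less weight. The SAP's wording may leave room for other covariates, but the bracketed list reads as complete, and an open list would permit choices after the data are seen. SAP section 6 has the study team review in-hospital deaths at interim analyses; that is a useful safeguard, but it does not correct a model estimate and does not cover the other three outcomes.

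**Conclusion.** The point holds for age and is of minor to moderate importance. As written, the safety models do not list a baseline variable that the trial collects and that the protocol itself offers as an example for adjustment. The exposure is to hospital-specific changes over time only; stable differences are absorbed, and so are common trends provided time is fitted as period.

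Under the assumptions above, a single-hospital shift of 1 to 3 years biases the pooled odds ratio by roughly 0.3 to 5% in either direction, reaching 6 to 7% only for a 3-year shift at the last hospital with an odds ratio of 1.8 per 10 years. The 15 to 18% figure is a worst case, with a 3-year shift at every hospital's own crossover. Nothing in the documents suggests that pattern, so it should not be read as the expected bias. All these figures ignore the overlap between age and the Elixhauser index.

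**What to change.** In SAP section 7, add age as a continuous covariate, preferably as a spline, to all four safety models, and report the model without age as a sensitivity analysis. Add sex as well if it is extracted; the protocol names it as an example, but SAP section 5 does not list it. In the same edit, state that time in the safety models means the bimonthly period, as in the primary model, or say what else is intended.

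The cost is a line or two of SAP text. Age is already in the planned extraction, so no new data collection is needed for it, and the adjustment has no evident downside.
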